**Fig. 2 Fig2:**
[figure not shown]
Standard Protocol Items: Recommendations for Interventional Trials (SPIRIT) figure

### Intervention

#### Experimental intervention program

The experimental group will receive a modified physiotherapeutic scoliosis-specific exercise intervention: the three-dimensionally integrated exercise for scoliosis program, which includes autocorrection in three dimensions, postural correction, breathing training, resistance training, muscle fascia releasing, functional activities, balance training, core stability training, proprioceptive input exercises, and patient education. Autocorrection exercise in three dimensions will be combined with specific breathing mode, and isometric contraction training to correct abnormal spinal physiological curvatures in the sagittal plane, accompanied by a wedge pad to modify humpback, waist asymmetry, and pelvic rotation in the horizontal plane. In breathing pattern training, the physical therapist will stimulate the concave areas of the thorax for patients during deep inspiration and will transfer stimulation to the convex side during deep expiration. While the patient is in coronal plane with longitudinal axial stretching, pelvic adjustments will be made to reduce the lateral curvature. During this period, the physical therapist will teach the patient how to combine these exercises with activities of daily living. All the patients in the experimental arm will receive treatment of one or two sessions weekly in the hospital under the supervision of a physiotherapist and one session per day at home under parental supervision. Some examples are shown in Fig. 3.

**Fig. 3 Fig3:**
[figure not shown]
Examples of three-dimensionally integrated exercise for scoliosis

The physical therapist has 3 years of scoliosis therapy experience and will provide 95% of the therapy sessions. Another certified physical therapist will fill in as needed.

### Control group program

Control subjects will receive the standard of care according to the SRS criteria: observation for patients with curves between 10 degrees and 25 degrees [9] and attendance at the study assessments. The control group will only attend study assessments and not the therapy sessions.

### Compliance supervision

Compliance will be monitored using a home training diary to record the time and frequency of every-day home training, verified daily by a parent and weekly by a therapist. Meanwhile, all the patients will be added to Micro Message Platform app created by the research assistant. The assistant will divide the patients into two groups following their allocation and check the daily training at irregular intervals, answer patients’ questions online, share health knowledge with the patients, or remind the patients to attend clinic visits after the 6-month intervention. To maximize compliance, the physical therapist will provide home equipment, provide the patients with access to facilities, change the exercises to improve compliance with exercises to avoid patients’ getting bored with always performing the same exercises, and encourage parents to be fully engaged to ensure the exercises are regularly performed at home. Attendance will be calculated as a percentage of the prescribed visits attended, and compliance will be calculated as a percentage of the prescribed home exercise dose completed over the course of the 6 months of treatment. When compliance drops below 70%, the physical therapist will try to resolve the issues cooperatively with patients and parents [29, 30].

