### Study design

The present study is a randomized controlled trial (RCT) comparing a 6-month three-dimensionally integrated exercise for scoliosis intervention with a standard of care of observation alone (control group). The protocol conforms to Consolidated Standards of Reporting Trials (CONSORT) guidelines for nonpharmacological studies [27, 28] and the World Health Organization Trial Registration Data Set Version 1.2.1 guidelines for clinical trials protocols (See in Table 1 and Additional file 1). The study is being conducted at the Department of Rehabilitation Medicine, Xinhua Hospital affiliated to Shanghai Jiao Tong University School of Medicine, China. A trained research assistant who is blinded to the randomization design will invite eligible patients to attend the specific scoliosis clinic to participate in the study. The physician in the clinic will explain the whole protocol in the quiet clinic room and obtain written informed consent from each participant and legal representative prior to inclusion. The trial profile is displayed in Fig. 1.

**Table 1 Tab1:** World Health Organization Trial Registration Data Set (Version 1.2.1)

Item number	Item	Description	Addressed on page number
1	Primary registry and trial identifying number	Name of primary registry and the unique identifier assigned by the primary registry	3
2	Date of registration in primary registry	Date when the trial was officially registered in the primary registry	3
3	Secondary identifying numbers	Other identifiers, if any Universal Trial Number Identifiers assigned by the sponsor Other trial registration numbers issued by other registries Identifiers issued by funding bodies, collaborative research groups, regulatory authorities, ethics committees/institutional review boards, etc.	Not applicable
4	Sources of monetary or material support	Major sources of monetary or material support for the trial (for example, funding agency, foundation, company, and institution)	17
5	Primary sponsor	Person, organization, group, or other legal entity that takes responsibility for initiating and managing a study	17
6	Secondary sponsor(s)	Additional persons, organizations, or other legal persons, if any, who have agreed with the primary sponsor to take on responsibilities of sponsorship	Not applicable
7	Contact for public queries	E-mail address, telephone number, and postal address of the contact who will respond to general queries, including information about current recruitment status	2

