### Randomization and masking

After an initial assessment examination confirming eligibility and collection of baseline data, participants will be allocated by a physician using computer-generated block randomization in a ratio of 1:1 to the experimental group or control group. The allocations will be concealed in sequentially numbered, opaque, sealed envelopes with a signature across the sealing point.

Because of the nature of the intervention, physical therapists and patients cannot be blinded when offering or receiving the treatment. However, patients will be asked not to reveal their group allocation to ensure blinding of the evaluator. To minimize bias, strict eligibility will be maintained in the whole trial, and there are separate rooms for assessment and treatment, so that each group will hardly know much about each other. A trained evaluator blinded to group allocation will complete all patient assessments at baseline and immediately after the 6-month intervention. Both groups will continue with their routine activities, but they will not be able to attend any other formal exercise program. The statistician will not be aware of the data coding. Figure 2 illustrates the timing of all trial processes (Additional file 2).

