## Discussion

This study protocol describes an RCT that is designed to evaluate the efficacy of three-dimensionally integrated exercise on scoliosis measured as Cobb angle, the ATR in degrees, sagittal profile, and quality of life in patients with mild AIS.

In this study, the patients and intervention team are not blinded, because the intervention team needs to carry out the detailed treatment plan with the patients, and the patients in each group know their treatment plan. The assessor, enrollment assistant, and statisticians are blinded with respect to the patients’ treatment allocation. Meanwhile, there are separate rooms for assessment and treatment to avoid having other patients know about the treatment. The control group only needs to perform the assessment at the baseline and after the 6-month intervention, so they will have less time to communicate with the other patients. Once the patient asks to change the treatment plan, they will be eliminated from the study immediately.

Preventing the curve progression is the most important reason for treatment. There is still no intervention to cure AIS [1, 8]. The results of this RCT will provide valuable information for the family, patient, clinicians, and clinical decision makers, as well as to administrative stakeholders, and they may play an important role in providing healthcare services.

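### Unless two assistants are meant, the assistant who invites patients and is declared blind also groups every patient by arm in the messaging app

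*Protocol article*

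**What the plan says.** Four places in the protocol article bear on this.

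- **Study design**, on who invites: "A trained research assistant who is blinded to the randomization design will invite eligible patients to attend the specific scoliosis clinic". A physician in the clinic then explains the trial and takes consent.
- **Discussion**, on who is blind: "The assessor, enrollment assistant, and statisticians are blinded with respect to the patients’ treatment allocation". Only the patients and the intervention team are described there as unblinded.
- **Compliance supervision**, on the app: "all the patients will be added to Micro Message Platform app created by the research assistant". The next sentence reads: "The assistant will divide the patients into two groups following their allocation and check the daily training at irregular intervals". The same assistant answers patients' questions online and reminds them of the clinic visit after the 6-month intervention.
- **Randomization and masking**, on allocation: "participants will be allocated by a physician using computer-generated block randomization in a ratio of 1:1". On concealment: "The allocations will be concealed in sequentially numbered, opaque, sealed envelopes with a signature across the sealing point". No block size is given.

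**The concern.** A person who sorts every patient by arm knows every patient's arm. The article introduces a research assistant who invites patients, later refers to the research assistant who runs the app, and describes nobody else with that title. Read as written, the inviter keeps a running list of past assignments.

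The list matters because allocation is blocked 1:1 at one centre. Sealed envelopes hide the next card, but they do not prevent inference from the cards already opened. An inviter who expects the next arm could, knowingly or not, time or choose invitations by curve size, skeletal maturity or a family's readiness to train. That would be selection before randomisation in a trial of 42. The protocol's own statistical section lists age, Risser sign and compliance among variables that may be associated with risk of progression. Separately, the final report would state as fact a blind that the procedures do not deliver.

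**Working it through.** **1. The roles side by side.**

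| Section | Role title | Task or claim |
|---|---|---|
| Study design | a research assistant | invites eligible patients; blind to the randomization design |
| Discussion | enrollment assistant | blind to allocation |
| Compliance supervision | the research assistant | creates the app, groups all patients by allocation, checks training |

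The first and third rows share a title. The first two share the recruiting function. Nothing separates the inviting task from the app task. All three statements can be true only if the app assistant and the inviting assistant are different people, which the article does not say.

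**2. Do the tasks overlap in time?** Recruitment began on 26 February 2018 and is ongoing in the article. The interim analysis is tied to the enrolment of 20 of the 42 patients, so entry is staggered. The training checks belong to each patient's 6 months of treatment. Grouping of early patients therefore overlaps with invitation of later ones, unless all 42 are invited before any is grouped.

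**3. How predictable is the next assignment?** The protocol gives no figure on this, so there is none to reproduce. Inputs: 1:1 blocks (Randomization and masking); 42 patients (sample size section); block sizes 2, 4, 6 and 8 (assumption, none stated).

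The best guess is the arm with more places left in the block, or a coin toss when they are equal. The chance of being right is averaged over all balanced sequences and all positions.

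- Block of 2: (0.5 + 1) / 2 = 0.750.
- Block of 4: position 1 gives 0.5. Position 2 gives 2/3. At position 3, the first two match with probability 1/3 (then certain) and differ with probability 2/3 (then 0.5), giving 1/3 + 1/3 = 2/3. Position 4 gives 1. Mean: (0.5 + 0.667 + 0.667 + 1) / 4 = 0.708.
- Blocks of 6 and 8, by enumeration: 0.683 and 0.666.

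A truly blind inviter is right 50% of the time.

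**4. Does it help if the inviter does not know the block size?** Only a little. Guessing whichever arm is behind needs no block size. Simulated over 42 patients, it is right 75%, 70%, 68% and 66% of the time for fixed blocks of 2, 4, 6 and 8, and about 68–72% for randomly mixed sizes. What block size adds is certainty. If it is known or inferred, the share of assignments known for sure is 50%, 33%, 25% and 20%.

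**5. What if other invited patients are still pending?** The inviter acts before the clinic visit, consent, eligibility check, baseline data and allocation. Suppose k earlier invitees are not yet allocated (k is an assumption, block size taken as known). Worked case, block of 4 and k = 1: positions 1 and 2 give 0.5 each. Position 3, with only the first assignment known, gives 2/3. Position 4, with the first two known, gives 1/3 + 1/3 = 2/3. Mean: 2.333 / 4 = 0.583. By the same enumeration:

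| Pending | Correct, blocks of 2 / 4 / 6 | Certain, blocks of 2 / 4 / 6 |
|---|---|---|
| 0 | 75% / 71% / 68% | 50% / 33% / 25% |
| 1 | 50% / 58% / 60% | 0% / 8% / 8% |
| 2 | 50% / 54% / 57% | 0% / 0% / 2% |

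The top row is a ceiling, and the advantage shrinks quickly below it. Invitees who decline weaken the link between an invitation and an envelope further.

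**The case against.** The strongest reply is that one person in both roles is inferred, not stated. The Discussion uses a different label, and a journal article commonly leaves staff delegation to the full protocol. This stands, and it makes the finding conditional. It does not remove it, because the article makes a positive blinding claim in two places and assigns a task that conflicts with it.

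Second, being blinded to the randomization design may well mean not knowing the block size. If so, certainty about any assignment would first require the block size to be inferred. The better-than-chance guess remains (step 4).

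Third, the inviter is several steps away from the envelope. The patients invited must already be eligible, a physician consents, a physician allocates, and the outcome evaluator is blinded. Age and Risser sign are candidate covariates, which would partly cover steering on maturity but not on motivation. All of this limits the harm.

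Fourth, the allocating physician also sees past assignments, and moving the app work does not change that. This is correct. Whether the same physician obtains consent is not stated, so nothing further is claimed here.

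A reader might go further and infer that the blind is certainly absent, that up to half of the 42 assignments are known in advance, or that a few steered patients would shift the result. The documents do not support these. The first needs one person in both roles. The second needs blocks of 2, a known block size and nobody pending. For the third, no shift in Cobb angle can be derived from anything in the article.

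**Conclusion.** The concern holds conditionally. Study design and the Discussion declare the inviting assistant blind, while Compliance supervision gives the research assistant the allocation of every patient. Unless two people are meant, the stated blind does not hold during recruitment.

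In size, the chance of guessing the next arm rises from 50% to at most about 66–75%. That range assumes blocks of 2 to 8, full sight of past assignments and no other invitee pending; with one or two pending it is 50–60% for blocks of 2 to 6. The route to bias is selective or timed invitation. There is no evidence of steering, and no size of bias is shown. The fault is worth correcting because it is cheap to remove and would otherwise put an inaccurate blinding statement into the report. It does not invalidate the trial.

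**What to change.** 1. State whether the inviting assistant and the app assistant are the same person. If they are two people, one clarifying sentence settles the contradiction.
2. If they are the same, move the app grouping, training checks and exercise questions to the physical therapist, who is already unblinded and already verifies the home diary weekly, or to anyone with no part in invitation.
3. Bar the inviting assistant from the app groups and the allocation list until the last patient is randomised.
4. Keep the block size from recruiting staff. Varying the block size is no substitute for steps 2 and 3: someone who sees past assignments is still right about 68–72% of the time with mixed sizes.
5. If the inviting assistant has already done the app work since recruitment began, withdraw the statement that the enrollment assistant is blinded, and report what was done.

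The cost is a short protocol change and the reassignment of an existing task, with slightly more app time for the therapist. No extra staff are needed.

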### Withdrawal criteria

The patients or their families will be allowed to withdraw from the study if they make such a request.

### Suspension criteria

In the interim analysis, clinical significance is defined as a 5-degree Cobb angle change, which is the reliability of radiographic examination and the international “gold standard” for minimally significant clinical change [31]. Decreasing or remaining in Cobb angle of 5 degrees means the treatment is successful, whereas increasing the Cobb angle to greater than 5 degrees is defined as failure of treatment [32]. There are no standard stopping criteria for specific exercise therapy outcome. Previous studies showed that there is a 40% failure rate for standard care (observation) [18]. In light of the clinical practice as well as the previous studies, the stopping criteria used in this protocol are as follows:If more than 40% of patients fail in either the experimental group with three-dimensionally integrated exercise for scoliosis or the control group, the trial will be ended, suggesting a change of treatment.During the whole study period, if the patient has significantly abnormal progression in clinical examination and the Cobb angle has reached ≥ 25 degrees, the patient (in either the experimental group or the control group) will be suspended from the study.

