### Interim analysis

An interim analysis will be performed on the primary endpoint of Cobb angle when enrolling 20 patients, including control group and experimental group, by a single statistician who is blinded to allocation and reports the results to the main investigators. The main investigators will discuss the results of the interim analysis with the monitoring board. In this study, the change of Cobb angle is the only primary outcome measurement; the secondary outcome measurements are the supporting elements for the whole outcome.

Our primary hypothesis is that the experimental intervention of three-dimensionally integrated exercise for scoliosis will optimize improvement in outcome effects (reduction in Cobb angle and improvement in multifidus activation). Effect sizes will be estimated using Cohen’s *d*, which corresponds to the mean difference between the groups in the change observed from baseline to 6 months (three-dimensionally integrated exercise for scoliosis standard of care), divided by the pooled SD at baseline (Cohen’s *d* ≥ 0.8 = large, 0.5–0.8 = moderate, 0.2–0.5 = small [45]). According to the previous study, the perceived mean global rating of change in the specific exercise group was 3.8 ± 2.2, corresponding to moderate improvement, and 0.3 ± 1.7 in the standard care group, corresponding to a small amount of deterioration [46]. In this study, an effect size change of 0.3 would be considered a significant finding to stop the study when performing the interim analysis [47]. The reasons for withdrawal from trial by arm will be calculated by the physical therapist.

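### The trial-ending failure trigger covers the control arm and is set at the same 40% failure rate that the protocol quotes for observation

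*Protocol article*

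**What the plan says.** Three parts of the protocol article bear on this point.

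- **Suspension criteria.** Failure is defined in these words: "increasing the Cobb angle to greater than 5 degrees is defined as failure of treatment". The section then gives the background rate: "Previous studies showed that there is a 40% failure rate for standard care (observation"). The trial-level rule follows: "If more than 40% of patients fail in either the experimental group" "or the control group, the trial will be ended, suggesting a change of treatment". A separate criterion, for suspending an individual patient, comes after it and is not at issue here.
- **When the rule is read.** The section opens by tying its definitions to the interim look: "In the interim analysis, clinical significance is defined as a 5-degree Cobb angle change". Interim analysis places that look "when enrolling 20 patients, including control group and experimental group". Randomization and masking specifies "computer-generated block randomization in a ratio of 1:1" and gives no block size.
- **Control treatment.** Control group program says that controls are observed and attend the study assessments only. The 40% quoted for observation is thus the protocol's own figure for the control arm.

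**The concern.** A trigger meant to show that an arm is doing badly should lie above what is expected of that arm. Here the limit for the control arm equals its quoted rate, so an unremarkable control arm crosses it often. The limit cannot separate controls doing worse than expected from controls doing as expected.

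The rule also looks at each arm alone. Many failures under observation with few under exercise is the pattern that the trial's hypothesis predicts, yet as written that pattern ends the trial. The trial could close about half recruited (20 of 42 patients) on a criterion that says nothing about whether exercise is better than observation.

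**Working it through.** The protocol gives no operating characteristic for this rule, so there is no stated figure to reproduce.

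**Inputs**
- Trigger: strictly more than 40% failures in an arm (Suspension criteria).
- Control failure rate: p = 0.40 (Suspension criteria).
- Controls with outcomes at the interim: n = 10. This is an assumption from 20 patients at 1:1. The look is defined by enrolment while outcomes come at 6 months, so the evaluable number could differ.
- Failure is read as an increase of more than 5 degrees. Taken literally, a final angle above 5 degrees would count nearly everyone, since entry requires 10 to 20 degrees.

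**Step 1: chance that the control arm alone triggers.** With n = 10, four failures are exactly 40% and do not trigger; five do.

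P(X ≥ 5 | 10, 0.40) = Σ C(10,k) 0.4^k 0.6^(10−k) for k = 5 to 10 = 0.2007 + 0.1115 + 0.0425 + 0.0106 + 0.0016 + 0.0001 = **0.367**.

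**Step 2: other numbers of evaluable controls, true rate 40%**

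| Controls | Failures needed | Probability |
|---|---|---|
| 5 | 3 | 31.7% |
| 6 | 3 | 45.6% |
| 7 | 3 | 58.0% |
| 8 | 4 | 40.6% |
| 9 | 4 | 51.7% |
| 10 | 5 | 36.7% |
| 11 | 5 | 46.7% |
| 12 | 5 | 56.2% |
| 21 | 9 | 47.6% |

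The figures move up and down because the count must be a whole number. More patients do not cure the problem: at 21 controls the chance is still about 48%.

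**Step 3: other true control rates, 10 controls.** P(X ≥ 5) is 25% at a rate of 35%, 15.0% at 30% and 4.0% at 21%.

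The 21% comes from the inputs in Sample measurement (control change 2.90, SD 2.60). Assuming normal changes, z = (5 − 2.90)/2.60 = 0.808, and P(change > 5) = 0.210. The same step for exercise (−1.55, SD 4.39) gives z = (5 + 1.55)/4.39 = 1.492, a failure rate of 0.068, and P(X ≥ 5 | 10) = 0.0003.

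**Step 4: either arm, 10 per arm.** P(stop) = 1 − (1 − a)(1 − b), where a and b are the two arms' tail probabilities.
- 40% failing in both arms: 1 − (1 − 0.367)² = 59.9%.
- Control 40%, exercise 20%: 1 − (0.633)(0.967) = 38.8%.
- Sample-size inputs in both arms: 1 − (0.9604)(0.9997) = about 4.0%.

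**The case against.** **The 37% is conditional.** It needs a true rate of 40% and 10 evaluable controls. This stands. A reader might infer that the trial simply has a 37% chance of ending. The documents do not support that: depending on the control rate and the number evaluable, the chance runs from about 4% to over 50%.

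**The two control-arm figures may not conflict.** A reader might infer that 40% and the roughly 21% from the sample-size inputs contradict each other. That is not established. Sample measurement takes its inputs from reference 25, which Background describes as a 3-month study. The 40% is cited to a different source with no follow-up time given. The 21% also rests on normality. Rates over different horizons can differ without either being wrong.

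**Which arm would trigger.** A reader might conclude that nearly every stop would come from the control arm. That pairs a 40% control rate from one section with a 7% exercise rate derived from another. If 40% failed in both arms, each would be equally likely to trigger.

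**The second interim rule.** Interim analysis also allows a stop at an effect size of 0.3. A reader might see two rules pulling in opposite directions. Both only stop the trial, so the lack of a stated precedence affects how a stop is interpreted, not whether it happens. It adds little here.

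**Board review and patient protection.** The interim does include a between-group effect size, and the investigators discuss the results with the monitoring board. The 40% rule may also be meant to protect minors. Both points are fair and bear on the remedy. Neither changes the text: the rule says that the trial will be ended, does not make this depend on the comparison or on the board's judgement, and sets its limit at the quoted control rate.

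**Conclusion.** The concern holds in a conditional form. The protocol quotes a 40% failure rate for observation and, in the same section, ends the whole trial if more than 40% of an arm fails, control arm included. This is a fault in a rule that is stated, not a detail left to an analysis plan.

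If the quoted 40% is the true control rate, the control arm alone ends the trial with probability about 37% with 10 evaluable controls, 37% to 56% for 8 to 12, and about 48% if read at 21. If the true 6-month rate is lower, the chance falls to about 15% at 30% and 4% at 21%, both with 10 controls. The low figures do not support the rule as justified, because they require a control rate other than the one given as its basis.

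The coincidence of trigger and quoted rate is certain from the text. The size of the false-stop risk is not, because the 6-month control rate and the evaluable number at the interim are not fixed in the document.

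**What to change.** - Reconcile the trial-level trigger with the quoted 40% control rate, so that a control arm performing as expected does not by itself end the trial.
- Have the existing monitoring board read the failure proportions as a between-arm comparison, alongside the effect size already planned for the interim.
- State how many patients per arm must have 6-month outcomes when the rule is read, and the resulting false-stop probability over a range of control failure rates.
- State the control failure rate assumed and its time horizon, and how it relates to the change scores used for the sample size.

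No clinical threshold is proposed, and the patient-level criterion is left as it is. The cost is revised protocol wording and a one-page table of operating characteristics; no additional data or patients are needed.
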